### Objectives and research hypothesis

The aim of our trial is to assess the effectiveness of comprehensive orthogeriatric care (SOG care model) versus standard orthopaedic care with treatment by orthopaedic surgeons only in patients undergoing primary THA and TKA. The SOG care model consists of a comprehensive geriatric assessment, appropriate preoperative intervention, fast-track surgery principle and multimodal perioperative care on a SOG unit. We examine the outcomes of randomly assigned patients with assessments on postoperative days 1 to 7, 4 to 6 weeks and 3 months after surgery. Because immobility is an immediate result of osteoarthritis (OA) and leads to long-term functional deterioration, we choose mobility as the primary outcome. The current report outlines the research design and protocol for evaluating this randomized controlled trial of a multimodal intervention in frail patients with hip and knee replacement.

We hypothesize that multimodal perioperative orthogeriatric co-management (SOG care model) can improve the mobility of patients with total hip and knee arthroplasty (measured by SPPB).

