## Methods/design

### Study design

The SOG study is a registered, monocentric, prospective, randomized controlled trial. This parallel group RCT with a total of 310 patients is intended to investigate the specially developed multimodal care model (SOG care model) for orthogeriatric patients with total hip and knee arthroplasty (intervention group), which already begins preoperatively, in comparison to the usual orthopaedic care without orthogeriatric co-management (control group). The study data will be collected preoperative, postoperative day 1 to 7, 4 to 6 weeks and 3 months after surgery. The duration of the study was originally planned for 3 years. Due to the Corona-19 pandemic, an extension to 3.5 years is expected to be necessary. The trial is registered at the German Clinical Trials Register and the registry platform for international clinical trials of the World Health Organization (WHO) under the same Main ID DRKS00024102. We used the Standard Protocol Items: Recommendations for Interventional Trials.

(SPIRIT) guidelines to guide the reporting of our trial protocol [23]. A SPIRIT Checklist is provided as Additional file 2, and a flow diagram is included as Fig. 1.

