### Sample size

The sample size calculation is based on the primary endpoint of the analysis - “Improvement of Mobility”, measured by Short Physical Performance Battery (SPPB). According to previous studies, the clinically relevant difference between the two groups is conservatively estimated at 0,5 points with an expected standard deviation of 1,48 points [24]. Due to a 1:1 randomization, the number of cases per group is 139 to achieve a power of 80% at a 5% significance level (Gpower). Taking into account a possible dropout rate of 10%, a total of 310 patients should to be randomized.

The patient is not informed about the result of the randomization. The allocation is only known to the team directly treating the patient. In particular, the investigators who perform the post-intervention testing are blinded. For the patients, blinding is ensured by the fact that the patients in the control group also receive physiotherapy after surgery. Furthermore, the planned length of stay in hospital is the same for both study groups. An interdisciplinary ward round is simulated, but without orthogeriatric care in the actual sense. Very rare circumstances that may lead to emergency intervention during the study, and therefore possibly emergency unblinding, may include unpredictable highly pathological, life-threatening assessment, examination or laboratory results.

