### Data analysis

The evaluation is carried out as an intention-to-treat analysis. Baseline demographic and clinical characteristics of the participants will be described using summary statistics (means, standard deviations and frequencies). Significance in differences will be tested using t-test for continuous variables with normal distribution, chi-square test for categorical variables and Mann-Whitney U-test for continuous variables with non-normal distribution. Normality of the distributions will be tested graphically. We will examine the difference preoperatively and postoperatively (3 days, 7 days, 4–6 weeks, 3 months) with regard to the primary outcome variable (SPPB score) in the intervention and control group, as well as between the groups (postoperatively). To assess significance in differences we will use paired-samples t-test. Although the random assignment of the patients should provide unbiased results, the need for an adjusted analysis will be considered. To this end, in order to account for potential confounders, we will consider general linear models (e.g. multivariate linear regression and analysis of covariance [42] to evaluate between-group differences in SPPB scores. The need for an adjusted analysis within generalized linear (mixed) models will be considered as well. Secondary endpoints will be analysed both descriptively and standardized within adjusted regression analyses. *P*-values *p* < 0,05 will be considered as statistically significant. Detailed sensitivity analyses are planned for all outcomes of the intervention. Potentially missing data will be completed using adapted techniques (e.g. multiple imputation).

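### The only test the protocol commits to for SPPB is a paired-samples t-test, which does not fit the comparison of two independent randomised arms that is the primary objective

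*Protocol article*

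**What the plan says.** The Study design section describes two independent arms: "This parallel group RCT with a total of 310 patients". Under Objectives and research hypothesis, the primary objective contrasts SOG care with standard care on mobility at four postoperative times. The Sample size section is built on the same contrast: "the clinically relevant difference between the two groups is conservatively estimated at 0,5 points", with an SD of 1.48, 1:1 allocation and 139 per group.

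The Data analysis section says four things about testing:

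- After the sentence on baseline characteristics, a general rule: "Significance in differences will be tested using t-test for continuous variables with normal distribution", with chi-square and Mann-Whitney tests for other variable types. SPPB is not mentioned there.
- For the primary outcome, differences before and after surgery will be examined for the "SPPB score) in the intervention and control group, as well as between the groups (postoperatively").
- Immediately afterwards: "To assess significance in differences we will use paired-samples t-test".
- Then, to deal with possible confounding: "we will consider general linear models (e.g. multivariate linear regression and analysis of covariance") for between-group differences in SPPB. Generalized linear (mixed) models are also to be considered if adjustment is needed.

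**The concern.** A paired t-test needs two measurements that belong together, such as one patient before and after surgery. It suits the within-arm part of the SPPB plan. It does not suit the between-arm part, because the arms hold different people and the stratified block randomisation creates no matched pairs. Yet the sentence naming the test comes directly after one that covers both parts and makes no exception.

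At stake is the primary inference. Taken literally, the sentence assigns the trial's main question a test that the design cannot supply with pairs. If the paired test is taken to cover only the before-after part, the SPPB text contains no firm between-arm test. The analyst could then choose among an unadjusted test, ANCOVA and a mixed model after seeing the data. The SPPB p-values that are firmly promised would be before-after ones, and those do not measure what SOG care adds.

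**Working it through.** **1. Which test the sample size belongs to.** Inputs from the Sample size section: difference 0.5, SD 1.48, power 80%, significance level 5%, 1:1 allocation, dropout 10%. Sidedness is not stated.

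- Standardised difference: 0.5 / 1.48 = 0.338.
- Independent two-sample t-test, two-sided 5%, noncentral t: n = 138.5 per group, so **139**. This is the protocol's figure. Power at 139 per group is 0.801.
- Dropout: 139 / 0.9 = 154.4, so 155 per arm and 2 × 155 = **310**. This is the protocol's total.
- One-sided independent test: about 109 per group. No match.
- Paired t-test, reading 1.48 as the SD of the paired differences: 70.7, so **71 pairs**. No match.
- Paired t-test on arbitrary, uncorrelated cross-arm pairs: SD of differences = 1.48 × √2 = 2.093, n = 139.5, so 140 pairs. This is close, as theory says it should be, but is not the stated 139.

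The stated figures are those of a two-sided independent-groups test.

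**2. Which test the text commits to for SPPB.**

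| Statement in Data analysis | Tied to SPPB? | Firm? | Suits the between-arm contrast? |
|---|---|---|---|
| General t-test / chi-square / Mann-Whitney rule | No; follows the baseline description | Yes | Yes, if it were meant to apply |
| Paired-samples t-test | Yes; follows the SPPB sentence | Yes | No |
| Linear models, ANCOVA | Yes | No; to be considered | Yes |
| Generalized linear (mixed) models | By context | No; need to be considered | Yes |

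The only row both tied to SPPB and firm is the one that does not suit the contrast.

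**3. Why within-arm p-values cannot stand in for it (illustration only).** Assume 139 per arm and the same true gain in both arms, so that there is no treatment effect. The documents give no SD of change; 1.48 is assumed first. If p is the power of the paired test in one arm, the chance that exactly one arm is significant is 2p(1 − p).

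- Gain 0.25: p = 0.507, so 2 × 0.507 × 0.493 = 0.50.
- Gain 0.5: p = 0.977, so 2 × 0.977 × 0.023 = 0.045. Here both arms are usually significant although SOG adds nothing.
- Gain 0.25 with an assumed SD of change of 2.09 or 2.5: 0.41 and 0.34.

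In 5,000 simulated trials for each gain at SD 1.48, an independent test of the same data rejected in about 5%, as it should.

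**The case against.** The strongest reply is that this is a drafting slip in a section that otherwise points the right way. The objective and the sample size are plainly between-arm, a postoperative comparison between the groups is announced, and ANCOVA is named for exactly that purpose. The general t-test rule, listed with the Mann-Whitney test for independent groups, could be read as covering the group comparison, leaving the paired test for before-after change. A fuller analysis plan may exist.

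Much of this stands as an account of intent. It does not repair the text. The general rule follows the baseline description and is not linked to SPPB, ANCOVA is conditional, and the paired test is an explicit statement rather than a detail left to another document.

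Two stronger readings are tempting, and the documents do not support them:

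- **That efficacy will be judged by one arm being significant and the other not.** No such rule is stated, and a between-group comparison is explicitly planned. The 50% figure in step 3 is close to the maximum of 2p(1 − p), rests on an assumed gain and SD, and falls to 4.5% at a gain of 0.5 with the same SD. It is not an error rate of this trial.
- **That a paired test across arms would inflate the type I error.** With arbitrary pairing the mean difference still estimates the treatment effect, the test keeps its 5% level, and power at 139 pairs is 0.799 against 0.801. The objection is that such pairing is arbitrary, has no basis in the design and breaks down when dropout leaves the arms unequal.

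**Conclusion.** The statement is wrong as written and should be corrected before analysis. The protocol commits to a paired-samples t-test for SPPB where its objective, design and sample size all call for a comparison of independent groups. The fault lies in the test assigned, not in a missing comparison: suitable between-arm models are present but optional.

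The firm numerical evidence is the sample size, which reproduces as 139 per group for the independent test against 71 pairs for a paired test with the same inputs. The 71 depends on taking 1.48 as the SD of differences, which the protocol does not specify; the match at 139 assumes a two-sided test. No particular false-positive rate is claimed. The sample size itself needs no change.

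**What to change.** Replace the paired-test sentence with a committed primary analysis, for example:

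*The primary analysis is the difference in mean SPPB between the SOG and control arms at [the postoperative time designated as primary], estimated by ANCOVA with treatment arm, baseline SPPB and the randomisation strata (sex; hip or knee), reported with a 95% confidence interval and two-sided p-value. Changes from baseline within each arm are described without significance tests.*

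The sponsor has to fill in the time. The protocol lists four (day 3, day 7, 4 to 6 weeks, 3 months) and designates none as primary. A mixed model over the four times with one designated contrast is an acceptable alternative. The later wording on linear and mixed models should then be confined to supporting analyses.

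The cost is a short rewrite of the Data analysis section and one decision on the primary time or contrast. Baseline SPPB is already measured on admission, the strata are known at randomisation, and the total stays at 310. No extra patients or data are needed.

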### Randomization and consent

If the eligibility criteria are met, the patient has signed the information and consent form and the date for the surgery has been set, the participants will be randomized into the intervention or control group (usual care group). The random allocation sequence is performed computer-aided using a professional online tool for randomized clinical trials called “Randomizer” (https://www.randomizer.at/, Randomizer Version 2.1.0, Institute for Medical Informatics, Statistics and Documentation, Medical University of Graz). To ensure a balanced allocation sequence, a stratified permuted block randomization with stratification by gender (female or male) and type of care (knee or hip) will be used. We do not stratify by age, as only geriatric patients are included into the trial (age ≥ 70). The block sizes will not be disclosed, to ensure concealment. Thus, randomization will be conducted without any influence of the principal investigators, physicians, therapists, statisticians, or the research assistant.

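### Randomisation is stratified by sex and joint, but the tests named for the primary SPPB comparison ignore both factors, and adjustment and model type are left open

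*Protocol article*

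**What the plan says.** The Randomization and consent section sets out a "stratified permuted block randomization with stratification by gender (female or male) and type of care (knee or hip) will be used". It adds that age is not a stratification factor and gives the reason: "We do not stratify by age, as only geriatric patients are included into the trial".

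The Data analysis section opens with the baseline description: "Baseline demographic and clinical characteristics of the participants will be described using summary statistics (means, standard deviations and frequencies"). The next sentence reads "Significance in differences will be tested using t-test for continuous variables with normal distribution, chi-square test for categorical variables", and goes on to name the Mann-Whitney U-test. After a remark on checking normality, the section turns to SPPB, compared before and after surgery within each group and, postoperatively, between groups. The test given is: "To assess significance in differences we will use paired-samples t-test".

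Only then does adjustment appear: "Although the random assignment of the patients should provide unbiased results, the need for an adjusted analysis will be considered". The stated purpose is to deal with potential confounders, which are not named. Linear regression, analysis of covariance and generalized linear (mixed) models are each put forward for consideration. Neither sex nor joint is mentioned anywhere in the section. For secondary endpoints, by contrast, adjusted regression is a firm plan, although its covariates are not listed.

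**The concern.** Stratified blocks force the arms to be nearly equal on sex and joint. That removes from the treatment contrast the part of the chance variation that these factors would otherwise cause. A test that ignores the strata still counts that variation in its standard error. If sex or joint predicts SPPB, the standard error is too large, the confidence interval too wide and the test conservative. The design pays for precision that the analysis does not collect.

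The second issue is the open choice. The section makes the unadjusted analysis the default, with adjustment to follow if a need is seen, and gives no criterion for that need and no single model. Two analysts following it faithfully could report different primary results.

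Third, the significance tests come straight after the sentence on baseline characteristics, so the natural reading is that the randomised arms will be tested for baseline differences. Under proper randomisation such tests measure only chance, and they are a poor guide to whether to adjust.

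**Working it through.** **Inputs from the article (Sample size section).** Difference 0.5 SPPB points, SD 1.48, 1:1 allocation, 5% significance, 80% power, 139 per group, 10% dropout, 310 in total.

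**Assumed.** R², the share of SPPB variance explained by sex and joint together, is not given; it is varied from 0.05 to 0.20. The simulation below also assumes blocks of 4, 60% women and 50% hips.

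**Step 1: reproduce the plan's figure.** n per group = 2 × (1.960 + 0.842)² × 1.48² / 0.5² = 137.5, so 138. The t-distribution version gives 138.5, so 139, as stated. One-sided testing would give 109 and does not fit. 139 / 0.9 = 154.4, so 155 per arm and 310 in total. The sample size therefore rests on an unadjusted two-sided two-sample comparison.

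**Step 2: type I error when the strata are ignored.** With the strata balanced, the true standard error of the difference is about √(1 − R²) times the one that the unadjusted test uses. True type I error ≈ 2 × [1 − Φ(1.960 / √(1 − R²))].

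**Step 3: power at 139 per group.** Unadjusted SE = 1.48 × √(2/139) = 0.1775, and 0.5 / 0.1775 = 2.816.
- Unadjusted test: Φ((2.816 − 1.960) / √(1 − R²))
- Model with the strata: Φ(2.816 / √(1 − R²) − 1.960)

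| Assumed R² | Type I error, unadjusted | Power, unadjusted | Power, strata in model | Gain (points) |
|---|---|---|---|---|
| 0.05 | 4.4% | 81.0% | 82.4% | 1.4 |
| 0.10 | 3.9% | 81.7% | 84.3% | 2.7 |
| 0.15 | 3.4% | 82.4% | 86.3% | 4.0 |
| 0.20 | 2.8% | 83.1% | 88.3% | 5.2 |

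**Step 4: check by simulation.** 4,000 trials per setting, 278 patients, four sex-by-joint strata. For R² of 0.05, 0.10 and 0.20:
- type I error, unadjusted: 4.5%, 4.0% and 3.1%;
- type I error, strata in the model: 5.0%, 5.1% and 5.2%;
- power: 80.9% to 82.3%, 82.0% to 84.6%, and 82.6% to 87.8%.

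This agrees with the formulas within simulation error.

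**Step 5: what an open model could do.** If the most favourable of three results were reported (unadjusted; strata; strata plus a further covariate explaining an assumed 25% of variance), type I error was 7.3% to 7.7%. When the further covariate explained nothing and the strata 10%, it was 5.1%. The inflation thus depends on a strong optional covariate being available and on choosing by result. It is a worst case, not a forecast.

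**Step 6: can admission SPPB serve as the covariate?** Randomisation follows once the surgery date is set (Randomization and consent). Preoperative measures are delivered after randomisation (Study setting; Appropriate preoperative intervention). SPPB is first measured on hospital admission (Preoperative/inpatient admission; Primary outcome). It can therefore already carry part of the treatment effect. Sex, joint and age cannot.

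**The case against.** The strongest reply is that this is a journal article and that covariate lists belong in an analysis plan. That stands in part: a missing list alone would be no finding. But the article does state a rule, namely tests without strata first and adjustment if a need is seen, and for a stratified trial that rule is poorly fixed.

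It is also fair that R² is assumed, that at 5% the gain is under two power points, and that the unadjusted test still meets the planned 80% without raising false positives. This limits the size of the point but does not remove it.

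The sentence naming the t-test does not itself contain the word baseline and could be a general statement on group comparisons. Either way, none of the tests named uses the strata. The paired-samples test listed for SPPB is a separate problem, because it cannot compare two independent groups; the calculation uses the two-sample test on which the sample size rests.

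A reader might infer more than the article supports:
- **That baseline tests will select the covariates.** The article does not say so; the adjustment sentence comes several sentences later and gives no criterion. The article also says that the analysis is done externally and independently.
- **That adjustment is merely optional throughout.** For secondary endpoints it is firmly planned.
- **That leaving age out of the strata is a fault.** It is an explained and legitimate choice. Age is at most a useful covariate.

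**Conclusion.** The point holds for the primary SPPB comparison. The stratification factors are absent from the stated analysis, and adjustment and model type are undecided. The loss of precision is modest: about 1.5 to 5 power points, with type I error between about 4.5% and 3%, if sex and joint explain 5% to 20% of SPPB variance. At the lower end it is small. It would be wrong to conclude that the unadjusted result is biased or that the trial is underpowered. The greater risk to interpretation is the undecided model, whose effect on error rates cannot be fixed from the article. This should be changed, but it does not threaten the trial.

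**What to change.** In the analysis text, before any unblinded data are seen:

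1. State one primary between-group model for SPPB that always includes arm, sex and joint (hip or knee). Age may be added as a continuous covariate if this is fixed now.
2. Keep the unadjusted two-sample comparison, and label it a sensitivity analysis.
3. Put the same stratification factors into the adjusted regressions already planned for secondary endpoints, where event numbers allow. For rare outcomes such as mortality, a full covariate set may be unstable.
4. Report baseline characteristics by arm without significance tests, and do not use such tests to decide on adjustment.
5. Do not enter admission SPPB as though it had been measured before randomisation.

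Sex, joint and age are already collected and known before allocation, and the sample size of 310 stands. The cost is wording, plus some care with sparse secondary outcomes.

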### Ethical considerations

The study was approved by the ethics committee of the University of Regensburg (2020/06/24, No. 20–1837-101). Participants will undergo an informed consent process and sign a consent form prior to randomization. Patients recruited for the project will also be offered usual care.

## Discussion

The number of older patients undergoing elective orthopaedic surgery is increasing dramatically due to demographic change, advances in surgery and anaesthesia, and shifts in patient expectations of healthcare. As a result of the growing ageing of the population and the associated increased prevalence for degenerative joint diseases, a significant increase in total hip and knee arthroplasties in particular is predicted [5, 43]. Orthogeriatric co-management in traumatology has prevailed in the care of elderly, multimorbid patients with hip fractures. These patients benefit from significantly reduced morbidity and mortality as well as improved functional outcome and mobility [10, 12, 13, 17, 44]. However, previous orthogeriatric co-management models from traumatology have focused primarily on interdisciplinary care after surgery and have limited transferability to the care of elective orthopaedic patients.

Therefore, national and international orthopaedic and trauma societies have been calling for years for an extension of orthogeriatric care models to other, non-trauma-related musculoskeletal diseases. In addition to multiprofessional postoperative care of geriatric patients in traumatology, several other aspects are decisive for elective orthopaedic surgery of elderly patients with non-trauma-related diseases. Optimal preoperative preparation and reduction of surgical risk of multimorbid patients are of great importance in elective orthogeriatric care.

First of all, a reliable screening tool is needed to identify orthogeriatric patients. The ISAR screening tool [25], which is used in hospital emergency departments, is not suitable for elective patients. It is too non-specific. For this purpose, a separate screening tool (SOG screening tool) has been developed and is currently evaluated in the SOG study. An elementary component of the SOG care model is the preoperative involvement of a geriatrician after identification of an orthogeriatric patient. In this way, the preoperative risk assessment, the comprehensive geriatric assessment (CGA) and an appropriate preoperative intervention (API) can take place at an early stage and already in an interdisciplinary manner before the planned surgery. These approaches have already shown a significant benefit in postoperative outcomes after major surgery as a sole intervention in studies [45–48]. The SOG care model addresses several aspects in addition to optimal preoperative preparation of the patient and complex multiprofessional care after surgery. Patient blood management, anaesthesia, perioperative drug therapy, anticoagulation, standardized laboratory tests, crutch training, catheter avoidance, SOG unit, delirium prevention/delirium screening, orthopaedic-geriatric nursing, orthopaedic-geriatric ward rounds and common room for eating and socialising are further important components of the SOG care model. Another decisive element of the SOG concept is the surgical technique. Total hip and knee arthroplasty is carried out according to fast-track surgery principles, resulting in less pain and enabling early mobilisation. All these individual components together form the SOG care model.

We hypothesize that multimodal perioperative orthogeriatric co-management (SOG care model) can improve the mobility of patients with total hip and knee arthroplasty (measured by SPPB). In addition, further improvements in postoperative complications, delirium, cognition, mood, frailty, activities of daily living/instrumental activities of daily living, malnutrition, polypharmacy, length of hospital stay, rate of readmission to hospital, blood transfusion rate and other variables can be expected as a result of the multimodal intervention.

The proposed study has some limitations. Participant recruitment will take place within one hospital site, which may limit its generalizability to other hospital care settings. SOG investigators have considered the challenge of applicability to other settings during the study protocol development. The SOG care model is a complex, interdisciplinary intervention, but it also requires a functioning interaction of different professional groups in the hospital. A further limitation is the structurally impossible blinding of the staff on whose wards the concept is implemented. However, this could rather lead to a more preventive treatment of patients in the control group and to better results in standard orthopaedic care.

A major strength is the prospective randomized study design with 310 participants. The single centre model has the advantage that all patients are treated in the same way, thus reducing possible confounders. Other strengths of our proposed study include the use of valid and reliable measurements and the interdisciplinary involvement of all key professional groups involved in the implementation process. Some outcome measures can be compared or confirmed with other measures collected in the study. The primary outcome is physical functioning as measured by SPPB [30]. The SPPB has also been used in prior research to measure effects of interventions on physical functioning. In one study the SPPB was used to examine the effect of comprehensive geriatric care, compared to orthopaedic care, in the acute postoperative phase during hospital stay [44]. The SPPB was responsive and able to detect a difference between both groups even a few days after surgery. Our primary outcome measure is therefore considered to be sensitive to change, responsive and also used in other comparable studies. Our results are expected to be comparable to others, and this will strengthen the validity of the study. Measures with already known evidence-based benefits in the treatment of orthogeriatric patients with hip fractures were considered. PROM and PREM are also part of the study. The data analysis is carried out externally and independently at the Department of Health Economics, Technical University of Munich.

Medical Research Council (MRC) criteria define a “complex intervention” as interventions that are built up from a number of components, which may act both independently and inter-dependently [49]. These components include behaviors, behavior parameters, and methods of organizing those behaviors, and they may have an effect at the individual patient level, organizational, or service level or population level (or all of these in some cases) [49]. The present experimental intervention is considered to be a complex intervention. The outline for the arguments in this protocol is organized according to the guidelines of the Medical Research Council (MRC) guidance on how to develop and evaluate complex interventions [49].

The results of this prospective randomized controlled trial may, if successful, lead to the costs of the SOG care model being covered by health insurers in Germany and hospitals being able to use the SOG care model for orthogeriatric patients with knee and hip replacements, but also for other non-trauma-related musculoskeletal diseases. The results of this study will be presented as soon as they become available.

